### The oxford shoulder score

The Oxford Shoulder score constitutes of twelve questions specific to shoulder function subdivided in five different response levels. The score is presented in the Norwegian translation in Additional file 1 by appointment with Isis Innovation Limited (Project number 3240) and professor [name], University of Oxford, UK, who has contributed to the development of this test [69]. The score consists of twelve questions concerning shoulder function and activity of daily living, each question with five response levels. Scoring differ from 12 (worst) to 60 (best) points.

### Health related quality of life 15D

We use Harri Sintonen’s “15D”, a generic, self-administered instrument to assess Health Related Quality of Life (HRQoL) [63]. It encompasses 15 dimensions of health. The dimensions are moving, seeing, hearing, breathing, sleeping, eating, speech, eliminating, usual activities, mental function, feeling of discomfort, depression, distress, vitality and sexual activity. The questionnaire is modified, as the last dimension sexual activity is omitted, as some elderly patients may feel uncomfortable with this question. This score is validated and modifications in the statistical syntax for calculation of the score has been made to avoid confounding the outcome (http://www.15D-instrument.net). The scores along the 15 dimensions are translated into a zero-to-one quality of life index by means of an algorithm where zero represents death and 1.0 represents perfect health.

On admission to hospital, the patients will be asked to report their HRQoL as it was immediately before the fracture, and it will be repeated at 6 months, one, two and five years follow-up.

Quality adjusted life-years (QALYs) will be calculated for each patient by multiplying the time spent in a health-condition since the last follow-up by the HRQoL of this condition using the 15D scores (Additional file 1).

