#### Secondary objective

Quality of life will be measured with the 15D score [63], and calculations of QALY and cost during hospital stay and two years follow-up. Further outcomes are radiographic results and the Oxford shoulder score [64].

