### Statistics

Statistical analyses will be performed with the SPSS 17.0 software or later version (SPSS Inc. Chicago, Illinois, USA). All outcomes will be reported as mean values and 95% confidence interval (95% CI) for both treatment groups and for each hospital separate, as well as for all hospitals together. In case of small data groups, bootstrapped 95% CI will be calcluated. Mean differences between the groups will be compared with independent *t*-test and Mann–Whitney test as appropriate at two and five years follow-up. Subgroup analyses for the two fracture groups B2 and C2 are planned to gain further information of effectiveness of treatment. Multiple imputation will be used to handle missing values. The QALY analysis from 15D outcome will be performed according to the specific 15D syntax for SPSS and completed with a one-way sensitivity analysis for each variable in the analysis.

The intention-to-treat principle will be adopted: Patients will be analysed according to their initial treatment group in case of cross over to the other group.

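### A pre-fracture 15D is collected, but the stated group comparisons do not adjust for it, which gives up precision on 15D and QALYs (secondary outcomes; a free improvement)

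*Protocol article*

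**What the plan says.** The section on 15D collects a baseline: "On admission to hospital, the patients will be asked to report their HRQoL as it was immediately before the fracture". The same instrument is repeated at 6 months and at one, two and five years.

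The Statistics section names the between-group method: "Mean differences between the groups will be compared with independent" t-test and Mann-Whitney "test as appropriate at two and five years follow-up". For reporting it says: "All outcomes will be reported as mean values and 95% confidence interval (95% CI) for both treatment groups".

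The QALY is formed by "multiplying the time spent in a health-condition since the last follow-up by the HRQoL of this condition using the 15D scores". The Secondary objective covers "calculations of QALY and cost during hospital stay and two years follow-up". Beyond the 15D syntax, the Statistics section says only that the QALY analysis will be "completed with a one-way sensitivity analysis for each variable in the analysis".

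No section names a covariate, a change from baseline or a regression model. The Method of randomization section stratifies by age and gender within hospital, not by pre-fracture 15D.

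**The concern.** The 15D is a generic score that includes seeing, hearing, breathing and mental function. In patients aged 65 to 85, part of its spread at follow-up probably reflects health that predates the fracture. The admission value measures that health on the same scale, so it is the obvious covariate, yet no stated comparison uses it.

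Two things follow. The interval for the treatment difference is wider than it needs to be. And if one arm happens to be healthier before the fracture, part of that head start stays in the observed difference. The two-year QALY difference is the effect side of the cost-effectiveness result, where a small absolute shift can matter.

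For the primary outcome, the protocol does use a within-patient reference, by subtracting the uninjured shoulder's Constant score. No equivalent step is stated for 15D, although its baseline is already collected.

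**Working it through.** **Inputs from the article** (Power of the trial and sample size): difference 10 points, SD 18, alpha 0.05, power 0.80, 51 per group, 60 per group recruited. These concern the Constant score. No SD, correlation, target difference or power is given for 15D or QALY.

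**The plan's own figure.** n = 2 × (1.960 + 0.842)² × 18² / 10² = 50.9, so 51 per group. It reproduces with a two-sided alpha. Allowing 15% loss, 51 / 0.85 = 60. Only the group size is carried forward below.

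**Chance imbalance at baseline.** The SE of the difference in mean pre-fracture 15D is SD × √(2/n).

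| n per group | SE | 95% range | P(difference beyond ±0.2 SD) |
|---|---|---|---|
| 51 | 0.198 SD | ±0.39 SD | 31% |
| 60 | 0.183 SD | ±0.36 SD | 27% |

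This ignores any balancing through the age and gender strata.

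**Precision for 15D at one time point.** Adjustment multiplies the variance of the group difference by 1 − ρ², where ρ is the baseline to follow-up correlation (assumed). The unadjusted group size that would give the same precision is 51 / (1 − ρ²).

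| ρ | 1 − ρ² | Variance cut | Equivalent n per group |
|---|---|---|---|
| 0.3 | 0.91 | 9% | 56 |
| 0.5 | 0.75 | 25% | 68 |
| 0.7 | 0.51 | 51% | 100 |

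Estimating the extra slope costs about 1% of variance (factor 1 + 1/98), so the cuts are marginally smaller in practice.

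**Illustration for the two-year QALY.** Assumptions: 15D SD 0.10, ρ = 0.5, correlation between follow-ups 0.7, and 15D at 0, 6, 12 and 24 months as in the 15D section. The QALY is a weighted sum of those four values, and the weights depend on how the accumulation rule is read. The slope of QALY on baseline is w₀ + 0.5 × (w₆ + w₁₂ + w₂₄). A baseline difference of one SE is 0.10 × 0.198 = 0.020, and the 95% limit is 0.039.

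| Reading of the QALY rule | Weights (0, 6, 12, 24 months) | Slope | Shift at 1 SE | Shift at 95% limit | SE of difference, unadjusted → adjusted |
|---|---|---|---|---|---|
| Value at the end of each interval (baseline unused) | 0, 0.5, 0.5, 1 | 1.00 | 0.020 | 0.039 | 0.036 → 0.030 |
| Trapezoid | 0.25, 0.5, 0.75, 0.5 | 1.125 | 0.022 | 0.044 | 0.034 → 0.026 |
| Value at the start of each interval (baseline covers first 6 months) | 0.5, 0.5, 1, 0 | 1.25 | 0.025 | 0.049 | 0.034 → 0.023 |

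Over 15D SD 0.08 to 0.12 and ρ 0.3 to 0.7, the shift at the 95% limit runs from about 0.02 to 0.07 QALY. The imbalance reaches the QALY under every reading: through the correlation alone when baseline is unused, and also directly when it is used.

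**The case against.** The strongest reply is that nothing here is an error. Randomisation makes the unadjusted comparison unbiased on average, and its confidence interval already allows for chance imbalance. Stratification by age and gender may remove some of that imbalance. The outcomes are secondary, and the analysis plan and Additional file 1 are not shown. All of this stands. It limits the point to precision and to imbalance in the sample actually obtained. It does not remove the point, because for 15D at two and five years the article does name its tests, and they take no covariate.

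Some stronger readings are tempting and are not supported:

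- **That the QALY is built from follow-up values only.** The rule, "multiplying the time spent in a health-condition since the last follow-up by the HRQoL of this condition", does not say which value covers admission to 6 months. The pre-fracture value may be used there.
- **That the t-test is prescribed for QALYs.** The QALY has its own sentence in Statistics, which names no between-group test. One can say only that no baseline adjustment is stated.
- **That the unadjusted estimate is biased.** It is not, on average over randomisations.
- **That adjustment brings a known gain in power.** A figure could be produced from the Constant score's 10-point difference and SD of 18, but those belong to another endpoint and say nothing about 15D.
- **That the admission 15D is certain to precede allocation.** The timing makes this plausible: it is asked on admission, allocation follows consent, and enrolment may take up to 72 hours after admission. No section states it.

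The baseline is also a recalled value, which may weaken the correlation. At ρ = 0.3 the variance gain is only 9%.

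**Conclusion.** The point holds as a free improvement to a stated method. The trial collects a pre-fracture 15D, the named comparison at two and five years cannot use it, and no adjustment is stated for 15D or QALYs. The cost is lost precision, plus chance imbalance in pre-fracture health left in the estimate. The stated analysis remains valid.

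The size depends on quantities the article does not give. Across assumed correlations of 0.3 to 0.7, the variance of a 15D comparison falls by 9% to 51% (25% at 0.5). The SE of the chance baseline difference, about 0.20 SD at 51 per group, needs no such assumption. The QALY shifts are illustrative only, since they also rest on an assumed SD and follow-up correlation. The primary outcome and its sample size of 51 per group are untouched.

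**What to change.** In the Statistics section:

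1. Compare 15D at two and at five years, and QALYs over two years, by linear regression on treatment with the pre-fracture 15D as covariate.
2. Report the adjusted mean difference with its 95% CI.
3. Use the adjusted QALY difference in the cost-effectiveness analysis.

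In the 15D section, confirm that the admission questionnaire is completed before allocation, so that the covariate cannot be influenced by the assigned treatment. It would also help to state which 15D value covers the first 6 months of the QALY, although the case for adjustment does not depend on it.

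The cost is a few sentences and one regression per outcome in SPSS, which the trial already uses. There are no new data, visits or patients. The change should be fixed before outcomes are compared by group.

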### Radiographic evaluation

Initial radiographic examination will be performed with plain X-ray projections. These are:True antero-posterior projection.Scapula-Y projectionComputer-tomographic scans including 3D scans will also be performed to secure optimal classification pre-operatively, as the problem of intra- and inter-observer reproducability is a well known confounder of fracture classification in proximal humeral fractures [70, 71].

The fracture patterns will be classified according to the OTA/AO-system into types, groups and subgroups [19].

The medial hinge is measured on the initial radiographic examination. This is an important predictor of avascular humeral head necrosis as well as failure of fixation when treated with ORIF, as it offers mechanical support and maintain perfusion of the humeral head by the vessels in the posteromedial periosteum [51].

### Scoring of radiographs

Rating of implant position for RTSA and Philos plate will be according to figures in Additional file 1.

Radiographic evaluation by two independent reviewers is an important principle when radiographs are scored. All radiographs from all centers will be examined by the same two independent senior consultants: One experienced skeletal radiolog and one orthopaedic surgeon who had not participated in the surgical treatment of these patients. Scoring of radiographs from three and six months, one, two and five years will be performed. All radiographic measurements will be performed using the Siemens Magic Web 300 software.

### Important items for ORIF with Philos plate

Pre-operative:

Initial valgus or varus displacement (degrees°)Medial metaphyseal comminution, i.e. intermediate cortical fragment (Yes/No)Medial metaphyseal head extension in varus displacement (millimeters) [51]Medial hinge displacement in valgus displacement [51]

Post-operative and later follow-ups:

Humeral head inclinationPosition of greater tubercle and plate height. Displacement, resorption or healing.Alignment of the humeral head in glenoid fossa (central or acentric).“Sinking” of humeral head resulting in late screw tip penetration of joint surfaceAvascular head necrosis according to our former classification (Grade 0-1-2) [16]*.Failure of osteofixation (pull-out, cut-out)Non-union

*Definition of avascular humeral head necrosis as seen on plain X-ray projection will be:2 points: No changes1 point: Changes in normal trabecular organization engaging less than 50% of the humeral head in true AP view0 point: Partial collapse of the humeral head surface and-/or structural changes engaging more than 50% in true AP view.

### Important items for Reverse Total Shoulder Arthroplasty (RTSA)

Preoperative:

Metaphyseal comminution (cerclage wire around the metaphysis necessary?)Glenoid anteversion or retroversion

Postoperative and later follow-ups:

Notching will be evaluated according to Nerot score [72, 73]Grade 1: notch limited to the scapular pillarGrade 2: notch reaching the inferior screw of the base plateGrade 3: notch extending beyond the inferior screwGrade 4: notch reaching the base-plate’s central pegPosition of greater and lesser tubercles. Displacement, resorbtion or healingOssifications of the scapulohumeral spaceRadiolucent lines will be measured a) in seven different zones around the humeral stem, and b) beneath the glenoid baseplate and around the central peg and fixation screws [74] Additional file 1: Figure S3.Dislocation

### Economic evaluation

Cost data in this study will include costs incurred in hospital and subsequently, including time spent in operating theatre, hospital consumables, rehabilitation stays, subsequent hospital stay, help at home, consultations of NHS care (General practitioners, physiotherapists, district nurses etc.), transportation and sick-leave. Information for estimating costs will be collected from the patient by a questionnaire at each follow-up. Health-utility data will be obtained from the HS15D [63] (Additional file 1).

### Clinical follow-ups and blinding

The clinical follow-ups will take place at 3 and 6 months, one, two and five years. An independent physiotherapist will perform Constant scoring and assist the patients with a 15D QoL-questionnaire at these follow-ups. The physiotherapist will be blinded to the treatment and shall not take active part in the patient treatment of either group. The postoperative exercises and prescribed self-training program will be explained to patients by another physiotherapist before they are discharged from the hospital.

At every follow-up all patients will wear a T-shirt to cover their shoulders during examination by the physiotherapist performing the shoulder test. The patients will be thoroughly instructed not to tell the physiotherapist about their treatment.

Patients will complete the OSS and ASES self-assessment form at 6 months, one, two and five years follow-ups. Radiographic examination will be performed at every follow-up.

### Timeline - inclusion period

Inclusion started at January 2013. According to the Norwegian National Hospital Registry (http://www.NPR.no) approximately 400 patients sustaining a proximal humeral fracture are admitted in the including hospitals every year. At least 20% of these fractures are of a complex type according to the inclusion criterion, equaling 80 patients per year. We estimate that half of the patients will be eligible to inclusion; that is 40 patients/year. Inclusion of 120 patients should be completed during spring 2016.

### Interventions

Patients will be randomized to two groups, each of 60 patients:

Group 1 Sixty patients in the first group (intervention group) will be treated with a reversed total shoulder artroplasty (RTSA) of Delta type.

Group 2 Sixty patients in the second group (control group) will be operated with open reduction and internal fixation using a Philos plate and suture cerclages.

All patients will be enrolled in the study within 72 hours of hospital admission. Surgery will take place within 7 days thereafter.

### Description of treatment groups

#### Operative technique

Surgeons trained and experienced in the surgical technique before performing surgery on study participants, will perform all operations as a daytime procedure The surgeons skills and number of procedures from each center will be reported according to the criterias given by the Consort group.Open reduction and internal fixation (Philos plate)The goal of surgery is anatomical reduction of the fracture and fracture stabilization to allow early mobilization. Surgery is performed under general anaesthesia with the patient in a beach-chair position and fluoroscopic control. The standardized approach is the deltopectoral, and will be preferred to a lateral deltoid split. An atraumatic reduction with respect to vascularization of bone fragments will be emphasized [50]. The osteofixation will be performed with an angular stable locking plate (Philos, Synthes®, Switzerland). After identification of the tubercle fragments, three size No5 braided polyester sutures are introduced around the insertion of the supraspinatus, infraspinatus and subscapularis tendons. The humeral head fragment(s) will be adjusted to anatomical inclination and retroversion using two K-wires as “joy-sticks” and temporarily transfixed by K-wires. The superior part of the locking plate is placed no higher than 1 cm below the top of the greater tubercle, and lateral to the bicipital groove to avoid interference with the anterior branch of the humeral circumflex artery. Also support of the medial part of the surgical neck by the most inferior locking screws according to Kralinger will be paid attention [51]. If necessary, a small buttress plate will be used medially to enhance the fixation (Figure 1). To avoid perforation of the tip of locking screws into the joint space during healing of the fracture due to “sinking” of the humeral head fragment for intracapsular C-type fractures, the screw tip should have a “clear space” of 8–10 mm to the subchondral bone. The need for bone grafting from the ipsilateral iliac crest or a bone substitute to enhanche stability after desimpacting the humeral head in a valgus-depressed fracture will be judged during the surgical procedure. Fluoroscopic control of fracture alignment and implant positioning is performed throughout the procedure.

**Figure 1 Fig1:**
[figure not shown]
**Displaced proximal humeral fracture.** Control group. Angular stable implant (Philos) for osteofixation of a B2 varus fracture. 2.4 mm plate (Compact Foot, Synthez) has been used to secure the most frequent failure: Varus re-displacement.Reversed Total Shoulder Arthroplasty (Delta-Xtend prosthesis® from DePuy)The goals to be met are restoring proper biomechanics, achieving an optimal range of motion and minimize patient discomfort. The standardized approach is the delto-pectoral, preferred to the supero-lateral approach to prevent any damage of the deltoid muscle [75]. A cemented monobloc humeral stem will be implanted. An important point to adress is how to decide the correct height of the humeral stem in the fractured proximal humerus, thus establishing a proper tension and stability of the prosthesis to avoid complications as instability [76]. The perioperative judgment of stability using the trial-implants are therefore regarded important. Furthermore, the fixation of the greater and lesser tubercles is crucial, as optimal recovery after RTSA partly depend on reattachment of the tubercles [39, 77]. Braided polyester suture -cerclages (no 5) engaging the insertion of the subscapular and infraspinatus tendons will secure the tubercles using three 2 mm drill holes in the metaphyseal part of the shaft in addition to bone graft from the humeral head. If the surgical neck fracture extends further distal than the humerus metaphysis, a diaphyseal wire-cerclage will be applied to prevent further diaphyseal fracturing. Finally, prevention of the well known complication “scapular notching” is important, and the largest 42 mm glenosphere will be used to help creating an inferior prosthetic overhang against the scapular neck [62] (Figure 2).

**Figure 2 Fig2:**
[figure not shown]
**Displaced proximal humeral fracture: Intervention group: Delta prothesis with overhang of the inferior part of the glenosphere component and wire-cerclage to control concommittant metaphyseal fractures.**

### Postoperative rehabilitation and physiotherapy

#### Education prior to inclusion of patients

Physiotherapists and orthopaedic surgeons from all centers attended a short educational program before patient inclusion, consisting of a lectures as well as work-shops for all attending physiotherapists.

After surgery the operated upper extremity will be immobilized in a sling bandage. Both patients treated with Philos plate and with RTSA will start self exercises and supported physiotherapy during the first three postoperative days.

All patients will receive instructions regarding daily home exercises. During the period of immobilization, patients will be instructed to perform antioedema exercises of all joints distal to the shoulder. By discharge from the hospital, they will be taught a standardized self-exercise program to start immediately after the immobilization period.

Outclinic physiotherapists will be notified by the hospital physiotherapist to ensure that rehabilitation starts immediately after removal of the sling. All outclinic physiotherapists will receive guidelines for rehabilitation and physiotherapy of the trial patients. The patients are discharged from physiotherapy treatment when shoulder function is considered to be satisfactory or any further progression seems unlikely.

#### The physiotherapy training protocol

The physiotherapy guideline is mainly equal for the two groups. There is a difference in the timeline during the six first weeks after the surgery due to the fact that while a fracture operated with an angular stable plate should be regarded as stable for immediate training, a RTSA cannot be allowed rotation and resistance exercises for some period to allow healing of the tubercles. The main elements of physical therapy are outlined in Table 1.

For patients in the intervention group operated with reverse shoulder arthroplasty, the importance of healing of the tubercles without displacement is emphazised [37, 39]. Therefore these patients are given physical therapy with assisted exercises from the first to the the sixth week. Activating the deltoid muscle with assisted physiotherapy may be equally important, as this has to control and stabilize the prosthesis.

For patients treated with open reduction and osteofixation with the Philos plate and threaded cerclages, the proximal humerus is regarded stable for exercises immediately after operation with limitations against resistance exercises during the first 6 weeks after surgery.

Information to all included patients and attending health workers are electronically available at http://www.oslo-universitetssykehus.no/aktuelt_/prosjekter_/Sider/brudd-i-overarmsbenet.aspx.

